#### 11.4.2 Primary analysis

As a first step in this factorial trial, we will test for an interaction between the type of drug treatment and the monitoring type in order to assess if treatment effect is different depending on the type of monitoring. If the test is non-significant we will combine the two types of monitoring for the drug therapy comparison and the two drug therapies for the monitoring comparison. Otherwise, the trial will be analysed as a four-arm trial with a hierarchical testing approach.

For the primary comparison of the primary outcome between the two treatment arms, we will obtain the proportion of patients with viral suppression for 48 weeks in each arm, and compute a Mantel-Haenszel risk difference (DTG+FTC - cART) stratified for the monitoring type with a two-sided 95% confidence interval (107). If the lower confidence limit is higher than -12% we will conclude non-inferiority. If the lower confidence limit is below -12% we will conclude that DTG + FTC is potentially inferior to cART.

For the secondary comparison of the primary outcome between the two monitoring arms, we will calculate a Mantel-Haenszel test statistics and Mantel-Haenszel risk difference (DTG+FTC - cART) stratified for the type of treatment.

Secondary categorical outcomes (proportions of virological suppression <50 copies/mL both as a standard proportion and as FDA snapshot, of loss of future treatment options, of adverse events, of serious adverse events, of CSN adverse events, of CNS symptoms) between the DTG+FTC and cART groups, and between the patient-centered and standard monitoring groups will also be analysed using the Mantel-Haenszel test statistics and Mantel-Haenszel risk difference (DTG+FTC - cART) stratified for the type of monitoring and type of treatment, respectively.

For continuous outcome variables (CD4 count, HIV-DNA level, total cholesterol, high-density lipoproteine, triglycérides, low density lipoprotein-cholesterol, glucose, Framingham-calculated cardiovascular risk, glomerular function rate, weight, health-related quality of life, treatment satisfaction), we will compare the mean values at 48 months between the DTG+FTC and cART treatment groups and between the patient-centered and standard monitoring groups using linear regression adjusted for the type of monitoring and type of treatment, respectively.

Time to loss of virological response (TLOVR) will be graphically depicted by Kaplan-Meier curves, and evaluated by a univariable and multivariate Cox proportional Hazard model, adjusted for stratified for the type of monitoring and type of treatment.

Predictors of virological failure (nadir CD4 count, baseline HIV-DNA, zenith HIV-RNA, years since HIV infection, years of viral suppression, CD4/CD8 ratio, age, DTG and FTC plasma concentrations, pharmacogenetic analysis, any other relevant clinical or laboratory parameters) will be assessed using forward stepwise multiple logistic regression.

Economic analyses will be performed from the health provider perspective. A multiple linear regression model will be performed to compare the mean direct costs between the two monitoring strategies after adjustment for the treatment arm.

All analyses will be performed in the PP dataset and in the ITT dataset.

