| Number of Participants with Rationale: | 
Total number of participants: 184
 
Number in each group: 92
 
A sample size of 92 patients in each group (DTG + FTC dual therapy and standard cART) will be required to demonstrate non-inferiority with a non-inferiority (NI) margin of 12%.
                                                                                                                                                                                                                                                                                                                                                                                                                                                                                                                                                                                                                                                                                                                                                                                                                                                                                                                                                                                                                                                                                                                                                                                                                                                                                                                                                                                                                                                                                                                                                                |

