## **6. STUDY DESIGN**

### **6.1 General study design and justification of design**

This is a pragmatic multicentre, 2 x 2 factorial randomized controlled trial with 1:1:1:1 randomization to switching to DTG + FTC dual therapy or continuation of cART and to patient-centered monitoring or continuation of standard monitoring (Figure 4).

[figure not shown]

Figure 4: Schematic presentation of study design DTG + FTC dual therapy

HIV-infected patients virologically suppressed for at least 24 weeks on standard cART will be randomly allocated:

- Standard-of-care arm: patients randomized in this arm will continue their current cART regimen, according to section 7.1.
- Dual therapy arm: patients randomized in this arm will be switched to DTG + FTC dual therapy. DTG 50 mg and FTC 200 mg will be administered once daily as dual therapy for a duration of 48 weeks.

For all patients, HIV-RNA measurements will be performed at screening, baseline, week 6, week 12, and every 12 weeks afterwards. Any patient with HIV-RNA between 20 and 99 copies/ml at any time of scheduled visits will have an additional HIV-RNA measurement after 6 weeks ( $\pm 5$  days). Any patient with HIV-RNA  $> 100$  copies/ml at any time of scheduled visits will have an additional HIV-RNA measurement after 2 weeks ( $\pm 5$  days).

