### 11.2 Determination of Sample Size

The first sample size calculation was based on the primary outcome for the comparison between DTG + FTC dual therapy and standard cART, i.e. the comparison between the proportions of patients in the two arms maintaining virologic suppression, using a two-sample proportion test (96). The following assumptions were made:

- Power 80%
- Significance level 0.025 (one-sided Z test of non-inferiority)
- 97% of patients with conventional cART will be virologically suppressed at week 48 (<100 copies/ml)
- 94% of patients on DTG + FTC dual therapy will be virologically suppressed at week 48 (<100 copies/ml)
- Non-inferiority margin of 12% (as in previous non-inferiority trials)(97-104). We chose 12% noninferiority margin because there is no difference in terms of resistance acquisition between 10% and 22% virological failure.

Sample size of 83 patients in each group (total sample size, 166 patients) to achieve 80% power to detect a non-inferiority margin difference between the group proportions of -0.12 was calculated. The power was computed for the case when the actual cART group proportion is 97% and the actual DTG + FTC dual therapy group proportion is 94%. To allow for at least 10% loss to follow-up and also for the randomisation in two steps in this 1:1:1:1 trial, we will aim to recruit **a total of 184 patients**.

The second sample size calculation was based on the primary outcome for the comparison between simplified monitoring and standard monitoring, i.e. the comparison between mean direct costs in the two arms (105). The following assumptions were made:

- Significance level 0.05 (two-sided t-test)
- Direct costs are CHF 25,000 per year (standard deviation (SD) CHF 8,000) with conventional monitoring
- SDs are equal in the two groups (CHF 8,000)

With sample sizes of 92 patients in each group, we will have approximately 55% power to detect a 10% difference in costs, and 99% power to detect a 25% difference in costs. We will also have substantial power to detect small-to-moderate differences in many of the secondary outcomes, e.g. changes in CD4 cell counts or health-related quality of life. The exceptions are rare outcomes such as adverse events, resistance or clinical complications for which the statistical power to detect differences will be low.

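### An interaction pretest chooses between the powered pooled comparison and an unpowered four-arm analysis, and the monitoring risk difference is labelled so that it cannot be computed

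*Protocol*

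**What the plan says.** Protocol section 6.1 describes a "2 x 2 factorial randomized controlled trial with 1:1:1:1 randomization", and the synopsis gives "Total number of participants: 184", with 92 in each treatment group.

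Section 11.4.2 states that, as a first step, "we will test for an interaction between the type of drug treatment and the monitoring type". Two branches follow. In the first, "If the test is non-significant we will combine the two types of monitoring for the drug therapy comparison", and likewise the drug arms are combined for the monitoring comparison. In the second, "Otherwise, the trial will be analysed as a four-arm trial with a hierarchical testing approach". The section gives no level or scale for the test, and no order or success rule for the hierarchy.

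The primary comparison is then a Mantel-Haenszel risk difference stratified by monitoring type, with non-inferiority concluded if the lower 95% limit lies above -12%. The statistical considerations in the synopsis give this same analysis without any preceding test.

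Section 11.2 sizes the trial for two pooled groups: 97% v 94%, margin 12%, power 80%, "Significance level 0.025 (one-sided Z test of non-inferiority"), 83 per group, 184 recruited in total. Section 11.4.1 requires the per-protocol (PP) and intention-to-treat (ITT) analyses to reach the same conclusion.

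For virological suppression compared between monitoring arms, section 11.4.2 specifies "Mantel-Haenszel test statistics and Mantel-Haenszel risk difference (DTG+FTC - cART) stratified for the type of treatment". The next paragraph uses the same label for the secondary categorical outcomes of both comparisons.

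**The concern.** A preliminary test on the trial data decides which confirmatory analysis is run. Only one of the two possible analyses was sized. The deciding test compares two risk differences across four cells with few failures: about 92 x 0.03 + 92 x 0.06 = 8 in the whole trial at the design rates. Such a test will miss most interactions of a size that matters. When it does fire by chance, it replaces the powered comparison with comparisons of half the size. ITT and PP could also land in different branches, and the protocol has no rule for judging agreement between a pooled result and a four-arm result.

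The label problem is separate. Read literally, the monitoring comparison of the categorical outcomes asks for a treatment difference within each treatment group.

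**Working it through.** **Inputs.** From section 11.2: 97% and 94%, margin 12 points, one-sided 0.025. From section 6.1 and the synopsis: 1:1:1:1 and 184, hence 46 per cell. Assumed, because the protocol gives neither: a two-sided 0.05 interaction test (0.10 also run), on the risk-difference scale or on the log-odds scale with 0.5 added to each count. Simulations use four binomial cells of 46 and Wald limits; the pooled estimate is the equally weighted average of the two stratum differences.

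**1. The plan's own figure.** n = (1.960 + 0.842)² x (0.97 x 0.03 + 0.94 x 0.06) / (0.12 - 0.03)² = 7.849 x 0.0855 / 0.0081 = 82.8, so 83 per group. The stated sample size is reproduced, for the pooled comparison.

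**2. Non-inferiority power by branch** (normal approximation: Φ(0.09/SE - 1.96), SE = √(0.0855/n)).

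| Per arm | SE | Normal approximation | Simulated |
|---|---|---|---|
| 92 (pooled) | 0.0305 | 84% | 82% |
| 46 (one monitoring stratum) | 0.0431 | 55% | 57% |

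**3. Behaviour of the pretest.** The interaction SE is √(2 x 0.0855/46) = 0.061, twice the pooled SE. For 80% power the interaction must be about 2.80 x 0.061 = 0.17, or 17 points, which is larger than the margin.

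| Simulated trigger rate | Risk-difference scale | Log-odds scale |
|---|---|---|
| No interaction, level 0.05 | 5.6% | 0.6% |
| 10-point interaction, level 0.05 | 35% | 7% |
| 12-point interaction, level 0.05 | 45% | 10% |
| No interaction, level 0.10 | 11.7% | 3.4% |
| 12-point interaction, level 0.10 | 56% | 22% |

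The 12-point case is 97% v 97% under one monitoring type and 97% v 85% under the other.

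**4. The whole two-stage rule,** no interaction, risk-difference scale, level 0.05.

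- Always pooled: 81.7%.
- Pretest, then one pre-chosen stratum if triggered: 80.2%.
- Pretest, then both strata must pass if triggered: 77.7%.

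The loss is 1.5 to 4.0 points. On the log-odds scale the rule gives 81.2% to 81.5%, a loss of 0.2 to 0.5 points.

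**5. The monitoring contrast.** A Mantel-Haenszel risk difference weights stratum k by n1k·n0k/(n1k + n0k), where n1k and n0k are the numbers in the two groups compared. If the groups are DTG+FTC and cART and the strata are treatment, one of the two numbers is 0 in every stratum. Every weight is then 0 and the estimator is 0/0. With patient-centered and standard monitoring as the groups, each treatment stratum has 46 v 46 and the estimator exists.

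**The case against.** Several points on the other side are good.

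- **The pretest is not prone to false alarms.** Chance triggering of 5.6% or 0.6% is close to nominal or conservative. A reader might infer from the fall to 55-57% power that the trial as a whole is badly underpowered. It is not, since that fall applies only when the second branch is entered.
- **The pretest is not worthless.** It finds a 12-point interaction in nearly half of trials on the risk-difference scale, and a pooled average can conceal inferiority under one monitoring type. What stands is that detection is unreliable and depends strongly on an unstated scale, which is a weak basis for choosing the confirmatory analysis.
- **Sparse cells depend on the assumed rates.** At 97% v 94%, about half of trials have at least one cell with no failures. At the synopsis's 92% in both arms this falls to 8%. The protocol does not say the test is logistic, so it does not follow that the test could not be carried out.
- **Both strata passing.** The simulated chance is 33% overall, but about 8% once a chance trigger has occurred. The protocol does not say that both must pass, so neither figure is the power of the plan.
- **Details may be in the SAP.** Section 11.4.6 defers detail to that document, and the level, scale and order may be given there. The two-branch rule itself is fixed in the protocol.
- **The label is probably copied** from the preceding paragraph, and the intent is clear because the sentence names the monitoring arms. A reader might infer that the second primary outcome cannot be analysed. That is wrong: section 11.4.2 compares costs by linear regression adjusted for treatment arm, which is estimable.

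**Conclusion.** The point holds in a limited form. Section 11.4.2 gives an interaction test authority over the primary analysis, section 11.2 powers only one of the two branches, and the synopsis states the primary analysis with no such test.

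The expected cost in power is small: 81.7% to about 80.2%, or 77.7% if both strata must pass. This assumes 97% v 94%, 46 per cell, no interaction and a two-sided 0.05 test on the risk-difference scale. The stronger objection is one of principle: the confirmatory comparison is left to depend on a weak test of unstated level and scale, and ITT and PP could end in different branches.

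The monitoring risk difference, for virological suppression and for the secondary categorical outcomes, cannot be computed as labelled. That is a wording error, not a design flaw. Both items should be corrected before analysis.

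**What to change.** In section 11.4.2, make the Mantel-Haenszel risk difference stratified by monitoring type the primary analysis whatever the interaction result, in both ITT and PP, as the synopsis already implies. Report the interaction on the risk-difference scale with its 95% CI, together with the difference within each monitoring type, as supportive results.

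Reword the monitoring contrast as patient-centered minus standard monitoring, stratified by treatment, with a 95% CI, for virological suppression and for the secondary categorical outcomes.

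The cost is wording only, with no new data and no change in sample size. There is one downside: if a real interaction exists, the primary result is an average over the two monitoring types, so the stratum-specific differences must be shown beside it.

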#### ***HIV DNA reservoirs***

A challenge in HIV treatment is the existence of a HIV-DNA reservoir made of latently infected CD4 T-cells circulating in the peripheral blood or disseminated in lymphoid organs and associated tissues(19, 20). Sub-optimal drug penetration in tissues such as the genital tract or the brain may allow for ongoing replication in body compartments even with undetectable plasma viral load(21). The HIV-DNA reservoir establishes itself very early in the course of HIV infection(22), and is a strong predictor of HIV disease progression(23) as well as a risk factor for neurocognitive disorders(24). High level of HIV-DNA was predictive of virological rebound during ART interruptions(25). Some studies found that RAL decreased the HIV-DNA reservoir in latently infected peripheral T-cells when used in an intensification ART strategy(26) or when part of a conventional triple ART regimen(27).

The reservoir is measured by the total cell-associated HIV-DNA as the frequency of infected cells per million in peripheral blood mononuclear cells (PBMC)(20). Boulassel et al demonstrated that the CD4 cell nadir independently predicted the size of the HIV reservoir after prolonged therapy (28). In the current trial we will measure proviral DNA from PBMCs by using a novel digital droplet PCR based assay as developed in the laboratory of [name] / [name] at the University Hospital Zurich for the HIV.X project “Deciphering Host-Virus Interactions to Cure HIV” (29). We will also assess if proviral DNA, and nadir CD4 count, could predict virological failure.

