### 5.2 Secondary Outcomes

1. Proportion of patients maintaining HIV suppression defined as HIV-RNA <50 copies/ml throughout 48 weeks (+/- 21 days). A single blip defined as HIV-RNA <200 copies/ml during the study period is allowed as long as this value is followed by HIV-RNA <50 copies/ml;
2. Proportion of patients with HIV-RNA < 50 cp/ml at week 48 by FDA snapshot analysis; Proportion of patients experiencing loss of future drug options defined as new intermediate or high-level resistance to one or more drugs to which the patient's virus was considered sensitive at trial entry;
3. Time to loss of virological response (TLOVR) up to week 48 defined as the first of the two-confirmed HIV-RNA >100 copies/ml (at least two weeks apart);
4. Change in CD4 cell count from baseline to week 48 +/- 21 days;
5. Change in HIV-DNA level from baseline to week 48 +/- 21 days;
6. Change in lipidic profile (total cholesterol, high density lipoprotein-cholesterol, triglycerides, and low density lipoprotein-cholesterol) from baseline to week 48 +/- 21 days;
7. Change in glucose profile from baseline to week 48;
8. Change in Framingham-calculated cardiovascular risk from baseline to week 48;
9. Change in glomerular function rate from baseline to week 48;
10. Proportion of patients with an adverse event throughout week 48;
11. Proportion of patients with a serious adverse event (SAE) throughout week 48;
12. Proportion of patients with a CNS adverse event throughout week 48;
13. Proportion of patients new to DTG with CNS symptoms at 2 and 6 weeks after starting DTG;
14. Change in patients' health-related quality of life from baseline to weeks 12 and 48;
15. Assessment of patient's monitoring satisfaction from baseline to weeks 24 and 48 for patients in the patient-centered monitoring arm;
16. Assessment of the global satisfaction of the monitoring at week 48 for all patients (regardless of the randomisation arm);
17. Proportion of patients in the patient-centered monitoring arm expressing willingness to change monitoring options throughout 48 weeks;
18. Assessment of patient's treatment satisfaction at week 48;
19. Assessment of ARV treatment in the post study;
20. Study satisfaction at week 48;
21. Cost-effectiveness of study arms at 48 weeks;
22. Changes in patient weight from baseline to week 48.

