#### 11.4.3 Secondary analysis

For categorical outcomes, we will additionally calculate relative risk differences between groups. We will calculate odds ratios from multiple logistic regression models adjusting for the type of monitoring and type of treatment as appropriate. For repeatedly measured categorical outcome variables (virological suppression <50 copies/mL), we will consider a mixed effects logistic regression with a random intercept on the subject to account for within-patient correlations.

For repeatedly measured continuous outcome variables, we will also consider all measurements in a linear mixed effects regression model to account for within-patient correlations. Finally, we will analyse development over time by exploring the functional relationship between outcome and time using fractional polynomials and a treatment-by-time interaction term.

Moreover, we will evaluate all outcomes in crude analyses not adjusting for type of monitoring or type of treatment. Binary outcomes will be compared by the Chi-squared or Fisher's exact test, continuous outcomes by the Student t-test.

Cost-effectiveness of treatment arms (incremental cost-effectiveness ratio) will be calculated by taking the difference in mean costs between patient-centered arm and standard monitoring arm, and between DTG + FTC dual therapy arm and cART arm, and dividing them by the difference in time to loss of virological response (TLOVR) between the study arms. Difference in TLOVR will be assessed by comparing the area under the patient-centered and standard monitoring Kaplan-Meier curves, and under the DTG+FTC and cART Kaplan-Meier curves. Generalised lo-rank test will be used to compare times between groups.

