#### **11.4.6 Deviation(s) from the original statistical plan**

A statistical analysis plan will be written before the end of the first year of participants enrolment. It will describe in details the statistical analyses answering the primary research question but also answering secondary research questions. It will detail how data will be described depending on their format. Once data will be available, the statistician in charge of the statistical analyses will apply the statistical analysis plan. Any deviations from the planned analyses will be at least described and justified.

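### Section 11.4.2 compares final HIV-DNA and triglyceride means with no baseline term and no log scale named, which costs power for the reservoir outcome if HIV-DNA is widely spread

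*Protocol*

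**What the plan says.** Protocol section 11.4.2 treats all continuous outcomes alike. The list opens "For continuous outcome variables (CD4 count, HIV-DNA level, total cholesterol" and goes on to the other lipids including triglycerides, glucose, weight, quality of life and others. For all of them, "we will compare the mean values at 48 months between the DTG+FTC and cART treatment groups", and likewise between the monitoring groups, "using linear regression adjusted for the type of monitoring and type of treatment, respectively". The summary (a mean), the model and the only covariate are therefore stated. The unit of months is evidently a slip for weeks, since follow-up in the trial lasts 48 weeks.

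Section 11.4.3 adds crude comparisons, with "continuous outcomes by the Student t-test", and says that linear mixed models will be considered for repeated measurements. It names no transformation for these outcomes either.

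Section 5.2 defines the outcomes differently. Item 5 is "Change in HIV-DNA level from baseline to week 48 +/- 21 days", and item 6 covers change in the lipid profile, triglycerides included, over the same period. Section 3.1 describes the reservoir measure "as the frequency of infected cells per million in peripheral blood mononuclear cells (PBMC"), so the assay result is a frequency, not a log value. The study schedule collects HIV-DNA at day 0 and week 48, and lipids at screening and week 48, in both monitoring arms.

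Section 11.4.6 leaves detail to a statistical analysis plan: "It will detail how data will be described depending on their format". That plan is not at hand.

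**The concern.** Two features of the stated model look wrong for HIV-DNA.

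The first is scale. A frequency per million cells cannot fall below zero and may vary by multiples between patients. If so, the values are right-skewed, a few patients with large reservoirs carry much of the arm mean, and a proportional difference between arms is hard to see in a difference of means.

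The second is the missing baseline value. The outcome is defined as a change, the starting value is measured, and yet the model compares final values with no baseline term. All between-patient variation in reservoir size then stays in the error.

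At stake is whether the trial can say anything useful about the reservoir under two drugs. That is a secondary objective, and it uses a dedicated batch assay on stored cells at two visits. A null result could reflect the model and not the regimen.

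**Working it through.** **The protocol's own power figure.** Section 11.2 gives about 55% power for a 10% cost difference (CHF 2,500, SD CHF 8,000, 92 per arm, two-sided 5%). The normal approximation gives 56.3% and the noncentral t 55.9%, so the figure reproduces. No power, SD, distribution or expected effect is given for HIV-DNA or triglycerides.

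**Inputs for the check.**
- From section 11.2: 92 per arm; two-sided 5% as for the comparison of mean costs.
- Assumed, because the protocol gives none: log-normal values; a true ratio of 1.5 between arms; baseline to week 48 correlation 0.8 on the log scale; log10 SD from 0.2 to 0.7.

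**Log scale, by formula.** The effect is log10(1.5) = 0.176. The standard error is SD × √(2/92) = SD × 0.1474. Power is Φ(0.176/SE − 1.96).
- At SD 0.5, SE = 0.0737, 0.176/0.0737 = 2.39, and power = Φ(0.43) ≈ 67%.
- Adding the baseline value multiplies SE by √(1 − 0.8²) = 0.6. The ratio becomes 2.39/0.6 = 3.98, and power = Φ(2.02) ≈ 98%.

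**Untransformed scale.** This needs simulation of log-normal data. The simulated log-scale results agree with the formula to within about a percentage point.

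| log10 SD (assumed) | As written: untransformed, no baseline | log10, no baseline | log10 with baseline |
|---|---|---|---|
| 0.2 | 100% | 100% | 100% |
| 0.3 | 93% | 98% | 100% |
| 0.4 | 68% | 84% | 100% |
| 0.5 | 44% | 66% | 98% |
| 0.6 | 27% | 51% | 91% |
| 0.7 | 16% | 41% | 82% |

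**Splitting the gain.** At SD 0.5 the log scale alone adds 66 − 44 = 22 points, and the baseline covariate then adds 98 − 66 = 32. The baseline value on the untransformed scale gives 72/45/28% at SD 0.5/0.6/0.7, so neither change alone recovers what both together do.

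**Influence of high values.** Under the same log-normal assumption, the top 5% of patients carry about 12% of the arm total at SD 0.2, 24% at 0.4, 31% at 0.5 and 46% at 0.7.

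**Type I error.** With no true difference, the untransformed t-test rejects in 3.4 to 5.0% of simulated trials across this range. It is slightly conservative at the wide end and never inflated.

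**The case against.** The strongest objection is that the protocol never prescribes the raw scale. A reader might infer that it does, but the text says only that means will be compared by linear regression. A comparison of mean log10 values would comply with that wording. Transformation is ordinary content for a statistical analysis plan, and section 11.4.6 defers detail on secondary questions to one. This stands as a limit: the untransformed analysis is the plain reading of a mean of a level given per million cells, not an explicit instruction. It does not remove the point, because section 11.4.2 is not silent on the model. It states the summary and the covariates, and leaves out the baseline value for outcomes defined as change.

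Second, the size rests on assumed inputs. With a 1.2-fold difference and a log10 SD of 0.5 to 0.7, power without baseline is only 6 to 12% untransformed and 13 to 19% on the log scale, so the change of scale alone would not rescue the question. This also stands, and is why the range is shown and the conclusion is conditional.

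Third, triglycerides may have a narrow spread. If their log10 SD is 0.2 to 0.3 (also an assumption), the 1.5-fold setting loses 0 to 5 points without baseline. The triglyceride part is therefore a lesser point.

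Fourth, the mixed models in section 11.4.3 could bring in the baseline measurement. They are only to be considered, as a secondary analysis, and no scale is named there either.

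**Conclusion.** The point holds in a limited form. As stated, section 11.4.2 compares final means of HIV-DNA and triglycerides with no baseline term and no log scale, against outcomes that section 5.2 defines as change from baseline.

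For HIV-DNA the cost is material if the log10 SD is about 0.4 or more. Under the assumptions above, power falls from 100% to 68% at 0.4, from 98% to 44% at 0.5, and from 82% to 16% at 0.7, comparing log10 with baseline to the plan as written. At 0.2 to 0.3 the loss is 0 to 7 points.

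A reader might go further and infer that the plan certainly wastes most of its power, that triglycerides suffer equally, or that the trial's conclusions are at risk. The protocol does not support this. It gives no spread for either outcome, the loss may be small for triglycerides, and type I error is not inflated. These are secondary outcomes on which no primary conclusion depends.

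**What to change.** In section 11.4.2, take HIV-DNA out of the common list. Analyse log10 HIV-DNA at week 48 by linear regression on treatment arm, monitoring arm and the log10 baseline value, and report the ratio of geometric means with its 95% confidence interval. As a lesser point, do the same for triglycerides on the log scale, with the screening value as baseline. Correct the time unit in the same sentence.

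The rule for values below the detection limit can be left to the statistical analysis plan, provided that it is set before the analyst sees the batch assay results by arm.

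The cost is a sentence or two of text and no new data, since the baseline or screening values are already collected. The downside is that results are read as ratios instead of absolute differences.
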